## Abstract

*Background*. Acute carbon monoxide poisoning (ACOP) is a significant cause of morbidity and mortality in many countries. Twelve Hand Jing Points (THJP) have been believed to be effective to treat all kinds of emergency calls in traditional Chinese medicine (TCM) for more than 3000 years. This randomized controlled trial (RCT) is designed to evaluate the effectiveness of THJP in curing acute carbon monoxide poisoning in first aid treatment. This paper reports the protocol of the trial. * Methods/Design. *This RCT is a multicenter, randomized, controlled study undergoing in China. The compliant patients are divided into the bloodletting group and standard of care group. With first aid treatments given to both of the groups, the bloodletting group is bleeding at THJP upon being hospitalized. Primary outcomes and secondary outcomes will be measured and compared between these two groups. Before treatment, immediately after treatment, and 30 minutes, 1 hour, and 4 hours after treatment, patients' basic vital signs and state of consciousness were observed. Before treatment and 1 and 4 hours after treatment, carboxyhemoglobin concentration in venous blood samples was detected.* Discussion. *The objective of this study is to provide convincing evidence to clarify the efficacy and safety of THJP for early treatment of acute carbon monoxide poisoning.

## 1. Background

Acute carbon monoxide poisoning (ACOP) is a significant cause of morbidity and mortality in many countries, the rate of the largest number of poisoning accidental poisoning of life and occupational poisoning [1, 2]. It may account for more than half of the world fatal poisoning [3].

ACOP is rather common in winter of China. CO diffuses readily within the alveoli and has far greater affinity than oxygen for essential biological compounds such as hemoglobin and cellular oxidative enzymes. Thus, CO poisoning causes cellular hypoxia. However, the mechanisms of its complications remain unclear [4–6].

Although hyperbaric oxygen therapy (HBO) produces a larger reduction in carboxyhemoglobin half-life, its benefit is that risk ratio is still debated [7]. From the current research on acute carbon monoxide poisoning, researches on first aid measures right after the onset are few, but they can effectively solve hypoxia and protect the brain tissue [5].

Twelve Hand Jing Points are of the Chinese traditional medical first aid measures. They have been believed to treat all kinds of emergency for more than 3000 years. Previous studies have shown that THJP may be effective in the first aid treatment of acute carbon monoxide poisoning but have not provided conclusive evidence of THJP bloodletting for acute carbon monoxide poisoning [8]. Previous animal studies indicated that compared with the control group, the indicator of carboxyhemoglobin concentration and awaking time both significantly decreased with the mice receiving the THJP treatment with acute carbon monoxide poisoning [9, 10]. For this study, the objective is to clarify the efficacy and safety of THJP in first aid treatment of acute carbon monoxide poisoning.

## 2. Methods and Design

### 2.1. Design

This is a multicenter randomized controlled trial, enrolling both men and women with acute carbon monoxide poisoning in China. This study will be conducted at Neurosurgery and Neurology Hospital, Affiliated Hospital, Logistics University of the Chinese People's Armed Police Force; Wuqing Affiliated Hospital, Tianjin University of Traditional Chinese Medicine, and Tianjin Binhai New Area Dagang Hospital. The patient or the patient's family should write the informed consent for the study. The compliant patients according to visit order, by the method of central random [11], are divided into the bloodletting group and standard of care group. A designated researcher will provide patient groups, and acupuncturists do not know patient groups before treatment. The acupuncturists only know the group assignment prior to the treatment (see Figure 1).

This trial is financed by the National Natural Science Foundation of China (number 81303023). The research protocol has been approved by the Clinical Trial Ethics Committee of Affiliated Hospital of Logistics University of Chinese People's Armed Police Forces (trial registration number: ChiCTR-IOR-15005797).

### 2.2. Patients

#### 2.2.1. Study Population

Our study will include patients with acute carbon monoxide poisoning. To ensure the precision of results of this trial, patients who meet the following eligible criteria will be included in this study.

#### 2.2.2. Inclusion Criteria

Meeting the diagnostic criteria of GBZ23-2002 in acute carbon monoxide poisoning.The course of disease is within 6 hours.After the poisoning patients with disturbance of consciousness.

#### 2.2.3. Exclusion Criteria

Patients with delayed encephalopathy after acute carbon monoxide poisoning, cerebral hernia.Liver and kidney function in previous severe abnormality.Pregnant women, diabetes, and mental patients.The blood coagulation dysfunction.Doctors belief that there are some cases not suitable for inclusion.Being not followed up.

### 2.3. Intervention

#### 2.3.1. Standard of Care Group

The standard of care group will receive general first aid treatment including hyperbaric oxygen therapy (HBO) about 45–60 minutes, citicoline 1 g intravenously once daily, and naloxone 0.4 mg intravenously every 12 hours.

#### 2.3.2. Bloodletting Group

The bloodletting group will receive general first aid treatment, the same as control group. Meanwhile, the bloodletting group will be treated with THJP on admission immediately before hyperbaric oxygen therapy. The order of puncture and bloodletting should be set. In this study, we decide to puncture and bloodlet the left hand first and then the right hand in the order of Shaoshang (LU11), Shangyang (LI1), Zhongchong (PC9), Guan Chong (TE1), Shaochong (HT9), and Shaoze (S11). And the amount of bloodletting at each point is one drop. At the same time, we choose a unified model needle. The location of acupoints is as follows [12].

*Shaoshang (LU11)*. It is on the thumb, radial to the distal phalanx, 0.1 F-cun proximal-lateral to the radial corner of the thumb nail, at the intersection of the vertical line of the radial border and the horizontal line of the base of the thumb nail. 

*Shangyang (LI1)*. It is on the index finger, radial to the distal phalanx, 0.1 F-cun proximal-lateral to the radial corner of the index fingernail, at the intersection of the vertical line of the radial border of the fingernail and the horizontal line of the base of the index fingernail. 

*Zhongchong (PC9)*. It is on the middle finger, at the centre of the tip of the middle finger, 0.1 F-cun proximal-lateral to the radial corner of the thumbnail, at the intersection of the vertical line of the radial side of the nail and the horizontal line of the base of the finger nail. 

*Guan Chong (TE1)*. It is on the ring finger, ulnar to the distal phalanx, 0.1 F-cun proximal to the ulnar corner of the fingernail, at the intersection of the vertical line of the finger side of the nail and the horizontal line of the base of the finger nail. 

*Shaochong (HT9)*. It is on the little finger, radial to the distal phalanx, 0.1 F-cun proximal-lateral to the radial corner of the little finger nail, at the intersection of the vertical line of the radial border of the nail and the horizontal line of the base of the little finger nail. 

*Shaoze (S11)*. It is on the little finger, ulnar to the distal phalanx, 0.1 F-cun proximal-medial to the ulnar corner of the little finger nail, at the intersection of the vertical line of ulnar border of the nail and the horizontal line of the base of the little finger nail.

### 2.4. Outcome Measures

In this study, there are two primary outcomes and four secondary outcomes. These are presented in Table 1. Any adverse event resulting from THJP or adverse drug reaction will be recorded. Safety evaluation for THJP will be based on events which include hematoma, syncope, local infection, and any feelings of discomfort. Any adverse event resulting from THJP or adverse drug reaction to THJP will be recorded.

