#### 2.4.1. Primary Outcomes

Patients' states of consciousness (in Glasgow consciousness disorder table of GCS score) are observed at the following time points (before treatment, immediately after treatment, and 30 minutes, 1 hour, and 4 hours after treatment) in two groups. And patients' carboxyhemoglobin (COHb) concentration of venous blood samples is detected at the following time points (before treatment and 1 hour and 4 hours after treatment) in two groups.

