### 2.5. Sample Size and Statistical Analysis

Sample size will be based on the primary outcome. According to our pilot trial and review of the literature [8], the average defecation rate of patient with COHb was 22.40% with a standard deviation of 3.65% and the average defecation rate of patient with COHb was 17.78% with a standard deviation of 5.68%. To detect COHb% difference, we need a sample size of 30 in each group (*α* = 0.05, *β* = 0.10) [13]. To allow 5% for loss to follow-up, our proposed trial requires 62 patients (31 for each group).

Statistical analysis of all data will be done by Department of Public Health Statistics, which is blinded to this trial, using SPSS 19.0 software packages to analyze the data. All data are provided as mean ± standard deviation. The level of significance was set a *P* value less than 0.05. All of the analyses will be based on both an intention-to-treat analysis and a treated-per-protocol analysis. The intention-to-treat population was defined as the patients who are randomized and received at least one treatment session. The per-protocol population was defined as the patients who have no major protocol violations in the set. Both results of analysis will be compared to check whether the results are consistent.

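### Two primary outcomes, no decisive time point and no success rule: the stated 0.05 level does not fix the trial's false-positive rate, and only COHb is sized

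*Protocol article*

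**What the plan says.** - **Number of primaries.** Protocol article, section 2.4: "In this study, there are two primary outcomes and four secondary outcomes".
- **Readings.** Section 2.4.1 lists GCS as primary at these times: "before treatment, immediately after treatment, and 30 minutes, 1 hour, and 4 hours after treatment". That is four readings after treatment. COHb is primary before treatment and at 1 and 4 hours, so two readings after treatment. Table 1 shows the same schedule. Neither place singles out one time as decisive.
- **Sizing.** Section 2.5: "Sample size will be based on the primary outcome", in the singular. The planning figures are for COHb only: one mean "was 22.40% with a standard deviation of 3.65"%, the other 17.78% with a standard deviation of 5.68%. The time of measurement is not given. The result is 30 per group at α = 0.05 and β = 0.10. GCS has no planning figures.
- **Level.** Section 2.5: "The level of significance was set a *P* value less than 0.05". The article gives no division of this level, no order of testing, and no statement of whether one or both outcomes must succeed.

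**The concern.** Section 2.4 gives the trial two primary outcomes, and section 2.5 speaks of one. The number of primary endpoints, the time at which each is judged and what counts as success are design decisions, and the article leaves them unsettled while fixing one 0.05 threshold.

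Read plainly, a P value below 0.05 on either outcome could be reported as a positive primary result. The 0.05 would then describe a single test and not the trial's conclusion. If each time is also compared separately, there are six chances. In addition, a claim resting on GCS alone would rest on an outcome for which the article gives no power basis.

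**Working it through.** **Inputs from the article.** Two primary outcomes (2.4). Readings after treatment: 4 GCS + 2 COHb = 6 outcome-by-time readings at four distinct times (2.4.1, Table 1). Level 0.05, β = 0.10, COHb means 22.40% and 17.78%, SDs 3.65% and 5.68%, 30 per group (2.5).

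**Assumptions not in the article.** Two-sided tests, and the correlations between test statistics used below.

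**1. The plan's own sample size.** The difference is 22.40 − 17.78 = 4.62 points. The formula is n per group = 2(z₁₋α/₂ + z₁₋β)² SD²/4.62², with 1.960 + 1.282 = 3.242.

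- Both SDs: √((3.65² + 5.68²)/2) = 4.774. n = 2 × 3.242² × 4.774²/4.62² = 22.4, so 23 (24 by the t distribution). Power at 30 per group is 96.3%.
- Larger SD in both groups: n = 2 × 3.242² × 5.68²/4.62² = 31.8, so 32 (33 by t). Power at 30 is 88.3%.

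The stated 30 is matched only approximately, and more closely with the larger SD. The article does not say which SD was used, so both are carried forward.

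**2. False-positive rate when success on either outcome counts, one test per outcome.**

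- Independent tests: 1 − 0.95² = 9.75%.
- Correlation 0.5: 9.1%.
- Correlation 0.8: 7.8%.

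It falls to 5% only if the two tests are perfectly correlated.

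**3. False-positive rate when all six readings are tested separately and any one counts.** Independent tests: 1 − 0.95⁶ = 26.5%. With correlated statistics (simulation, 1,000,000 draws per setting, equal correlation within an outcome):

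| Correlation within an outcome | Correlation between outcomes | Rate |
|---|---|---|
| 0.5 | 0 to 0.3 | 23.3% to 22.4% |
| 0.7 | 0 to 0.5 | 20.3% to 18.4% |
| 0.9 | 0 to 0.5 | 15.8% to 14.5% |
| 0.95 | 0 to 0.5 | 14.0% to 12.9% |

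**4. False-positive rate when both outcomes must succeed (one test each at 0.05).** A false claim requires at least one true null hypothesis to be rejected at 0.05 while the other outcome also succeeds, so the rate is at most 5%.

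**5. Cost of splitting the level over two primaries (α = 0.05/2 = 0.025), for COHb.**

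| SD assumed | n per group for 90% power (normal approximation) | Power at 30, normal | Power at 30, t |
|---|---|---|---|
| 4.774 (both SDs) | 27 | 93.4% | 92.3% |
| 5.68 (both groups) | 38 | 81.8% | about 80% |

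**The case against.** The strongest reply is that a schedule of measurements is not a list of hypothesis tests. Section 2.4.1 says when GCS and COHb are recorded. Section 2.5 names no test or model, and one repeated-measures test per outcome would fit the text as well as six separate comparisons. The adjustment method, the testing order and the model are commonly left to an analysis plan or full protocol, and neither is shown. Sizing a trial on one of two primaries is common and no error in itself.

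Much of this stands. A reader might infer that six tests at 0.05 are planned and that the true error rate is some 15-23%. The documents do not support that as fact. It needs separate testing at each time, a rule that any one success suffices, and within-outcome correlations of about 0.5 to 0.9, and the article states none of these. Nor are there six time points: there are four, and six is the count of outcome-by-time readings. A reader might also bring in the acknowledged lack of blinding of patients and acupuncturists (section 3). The article does not say who scores GCS, and that question is separate from multiplicity.

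The reply does not reconcile sections 2.4 and 2.5 on how many primaries there are, nor supply a decisive time or a success rule. The article itself sets the primaries and the level, and even one test per outcome takes the rate above 5% if either counts.

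**Conclusion.** The point holds as a weakness in what the article fixes: two primary outcomes against a singular one in the sizing, no decisive time, and one 0.05 level with no success rule. Its size is conditional:

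- about 8-10% if either outcome counts and each has one test (correlation 0.8 down to independence);
- about 13-26.5% if all six readings are tested separately and any one counts (within-outcome correlation 0.95 down to independence);
- at most 5% if both outcomes must succeed.

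The text does not settle which case applies, and it gives no correlations to narrow the ranges.

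It would also go too far to say that splitting the level is free. At 0.025, 30 per group keeps 90% power for COHb if both planning SDs are used, but not if 5.68 applies to both groups.

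**What to change.** **Preferred.** In 2.4 and 2.5, name COHb at one stated time as the single primary endpoint, tested two-sided at 0.05. The time should be the one to which the 22.40% and 17.78% planning figures refer, and only the sponsor can say which that is. Test GCS at one named time only if COHb is significant, and call all other readings supportive. This matches the outcome on which the trial is sized. It needs no division of the level and no extra patients because of multiplicity.

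**If both outcomes stay primary.** Name one time for each and choose one rule:

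- Require both to succeed, each at 0.05. The power for joint success cannot exceed that for COHb alone and needs GCS planning figures, which the article does not give.
- Let either succeed, with Bonferroni (0.025 each) or Holm (smaller P value at 0.025, then the other at 0.05). Restate the power at the first-step level of 0.025 and say which SD is used. At 30 per group the COHb power is about 92% with both SDs and about 80% with 5.68 in both groups.

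**Cost.** A few sentences in 2.4 and 2.5 and a matching registry entry, settled before any outcome data are seen. The downside is that other time points can no longer be claimed as primary successes.

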## Figures and Tables

**Figure 1 fig1:**
[figure not shown]
Trail flow chart.

**Table 1 tab1:** Trial processes chart.

Times	Baseline		Treatment		
	−1	0	0.5 h	1 h	4 h
Patients					
Medical history	*√*				
Physical examination	*√*	*√*	*√*	*√*	*√*
Laboratory examination	*√*			*√*	*√*
Informed consent	*√*				
Randomization	*√*				
Intervention					
Standard of care group	General first aid treatment				
Bloodletting group	General first aid treatment + THJP				
*Outcome *					
primary outcomes					
GCS	*√*	*√*	*√*	*√*	*√*
COHb	*√*			*√*	*√*
Secondary outcomes					
T	*√*	*√*	*√*	*√*	*√*
P	*√*	*√*	*√*	*√*	*√*
R	*√*	*√*	*√*	*√*	*√*
BP	*√*	*√*	*√*	*√*	*√*
Trial evaluation					
Safety of hand pricking blood therapy	*√*	*√*	*√*	*√*	*√*
Adverse event	*√*	*√*	*√*	*√*	*√*
Reasons of drop-outs or withdrawals					*√*
Patient's compliance					*√*

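### Section 2.4 ties adverse-event recording to attribution while Table 1 does not, and scheduled safety checks stop at 4 h although local infection is a named safety event

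*Protocol article*

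**What the plan says.** The Background section makes safety an aim alongside efficacy: "the objective is to clarify the efficacy and safety of THJP in first aid treatment of acute carbon monoxide poisoning".

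Section 2.4 (Outcome Measures) then states what is to be recorded, twice and differently. One sentence reads "Any adverse event resulting from THJP or adverse drug reaction will be recorded". The other reads "Any adverse event resulting from THJP or adverse drug reaction to THJP will be recorded". Between them the section names the events on which the safety judgement rests: "Safety evaluation for THJP will be based on events which include hematoma, syncope, local infection, and any feelings of discomfort".

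Table 1 carries two safety rows under the trial-evaluation heading. One is "Safety of hand pricking blood therapy". The next is simply "Adverse event", with no qualification by arm or by cause. Both are ticked at −1, 0, 0.5 h, 1 h and 4 h, and 4 h is the last column.

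**The concern.** In a randomized trial, harm is best judged by counting events the same way in both arms and letting the comparison show what the added treatment contributes. A rule that records an event only once it has been attributed to that treatment puts a causal judgement before the count. This matters here because the patients are acutely poisoned and have disturbed consciousness. Syncope or deterioration could come from the poisoning, from the background treatment that both arms share, or from the bloodletting. If sites follow the prose of Section 2.4, the two arms would be observed under different rules.

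The second issue is timing. Local infection is one of four kinds of event named for the safety evaluation, yet no safety assessment is scheduled after 4 h. If an infection has not appeared by then, the schedule shown offers no later occasion to find it. What is at stake is the safety half of the objective, not the primary efficacy comparison.

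**Working it through.** There is no figure in the plan to reproduce on this point, so the check sets the places side by side.

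**Step 1: what each place would record in each arm.** Controls receive background care only (Section 2.3.1). The bloodletting arm receives the same care plus THJP (Section 2.3.2).

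| Source | Recordable in the bloodletting arm | Recordable in the control arm |
|---|---|---|
| Section 2.4, sentence without the restriction on drug reactions | Events attributed to THJP; any adverse drug reaction | Any adverse drug reaction |
| Section 2.4, sentence restricting drug reactions to THJP | Events or reactions attributed to THJP | None, read literally, because controls receive no THJP |
| Table 1, general adverse-event row | Any adverse event | Any adverse event |

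The three sources give three different rules. Only the Table 1 row treats the arms alike. Under either sentence of Section 2.4, an event that is neither a drug reaction nor blamed on THJP falls outside the stated rule. In the control arm that covers every event other than a drug reaction, at the least.

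**Step 2: what is captured regardless of attribution.** GCS (Section 2.4.1) and temperature, pulse, respiration and blood pressure (Section 2.4.2) are recorded in both groups at five time points: before treatment, immediately after, and at 30 minutes, 1 hour and 4 hours. Deterioration that shows in these measures up to 4 h can therefore be compared by arm. Events that do not show in them, such as hematoma or local infection, depend on the adverse-event rule.

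**Step 3: the observation window.** Section 2.3.2 gives six points on each hand, so 2 × 6 = 12 punctures per treated patient. The last column of Table 1 is 4 h, and the last time point in Sections 2.4.1 and 2.4.2 is also 4 h. The rows for drop-out reasons and compliance are ticked only at 4 h, which fits with its being the close of scheduled observation. Scheduled safety checks after 4 h: none.

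Whether 4 h is long enough for local infection cannot be derived from the article, which gives no onset time. As a matter of general reasoning, a puncture-site infection would seldom be visible that soon.

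**Step 4: whether a later check is feasible.** The background drugs in Section 2.3.1 are given once daily and every 12 hours. Both intervals exceed 4 h, so the article itself implies that patients remain under care after the last scheduled assessment.

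**The case against.** The strongest reply is that Table 1 already contains the right rule. Its general adverse-event row is ticked at every time point and limited neither by arm nor by cause, and Section 2.4 says that attributed events will be recorded without saying that others will not. This stands in part. A reader might infer from Section 2.4 that only attributed events are collected, or that the arms cannot be compared for safety at all. Table 1 and the unrestricted measurement of GCS and vital signs do not support that. What the reply does not do is remove the conflict: the only rule given in prose is the restrictive one, it appears twice, and a site following it would not produce comparable data.

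A second reply is that this is a condensed article, and reporting windows, causality procedures and follow-up of unresolved events may be in the full protocol. That is fair as to omissions. The article does not say that recording stops at 4 h, so a reader should not infer that a later infection would necessarily go unrecorded. The supportable statement is narrower: the schedule shown has no safety assessment after 4 h. The disagreement between text and table, however, is something the article states rather than leaves out.

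A reader might also infer that attribution is decided by unblinded staff. The Discussion says that patients and acupuncturists are not blinded, but the article does not say who judges causality, so this cannot be asserted. Nor is the tick at −1 for the safety of the pricking an error that can be shown, since it may be a baseline check.

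**Conclusion.** The point holds as an inconsistency to reconcile and a schedule that fits a named safety event poorly. Section 2.4 and Table 1 disagree on which adverse events are recorded, and the two sentences within Section 2.4 disagree on drug reactions. Under the prose rule the arms would not be observed on the same basis. Under any of the readings, the schedule shown ends at 4 h.

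The documents do not allow a numerical size. A reader might be tempted to cite the upper limit for an event rate when none is seen among 31 treated patients, but that limit follows from the number treated and would be the same with complete event recording and long follow-up. It does not measure this defect. The stronger conclusion, that the plan must show low harm whatever happens, is also not supported, because of the general row in Table 1.

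The conclusion rests on two assumptions: that sites would treat the prose of Section 2.4 as the operative rule unless told otherwise, and that local infection usually takes longer than 4 h to show. The efficacy analysis is not affected. The safety conclusion named as an objective is what would be poorly supported, and the remedy is cheap enough to be worth making.

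**What to change.** Replace the two recording sentences in Section 2.4 with a single rule that matches the general row of Table 1: all adverse events and deaths are recorded in both arms regardless of presumed cause, causality is noted afterwards as a separate item, and events are compared by arm. The listed THJP events can stay as events of special interest within that rule.

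Add one column to Table 1 for an adverse-event check in both arms at discharge, with inspection of the puncture sites in the bloodletting arm, so that local infection is looked for after 4 h.

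The cost is slightly more data entry and one check at discharge. The primary outcomes and the sample size do not change.

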#### 2.4.2. Secondary Outcomes

Patients' basic vital signs including temperature (*T*), pulse (*P*), respiration (*R*), and blood pressure (BP) are observed at the following time points (before treatment, immediately after treatment, and 30 minutes, 1 hour, and 4 hours after treatment) in two groups.

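### Syncope and discomfort, two of the four named THJP safety events, can be only partly ascertained in patients enrolled for disturbed consciousness, so their rates may be too low

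*Protocol article*

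**What the plan says.** Section 2.4 of the protocol article sets the basis for judging the safety of the intervention: "Safety evaluation for THJP will be based on events which include hematoma, syncope, local infection, and any feelings of discomfort". It adds a general rule: "Any adverse event resulting from THJP or adverse drug reaction to THJP will be recorded".

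One of the inclusion criteria in section 2.2.2 reads: "After the poisoning patients with disturbance of consciousness". No GCS limit or minimum severity is attached to it. Section 2.3.2 fixes the timing of the intervention: patients in that arm are "treated with THJP on admission immediately before hyperbaric oxygen therapy".

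GCS is a primary outcome, scored "before treatment, immediately after treatment, and 30 minutes, 1 hour, and 4 hours after treatment" (section 2.4.1). Temperature, pulse, respiration and blood pressure are secondary outcomes at the same five times (section 2.4.2). In Table 1, the row "Safety of hand pricking blood therapy" and a separate adverse-event row are ticked in all five columns. Section 2.5 plans 31 patients per arm.

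**The concern.** The named list suits an alert patient better than the one this trial enrols. Syncope is a transient loss of consciousness, and discomfort is known only if the patient expresses it. Every patient enters with impaired consciousness, and the puncture is done before hyperbaric oxygen has been given. Some patients will be unable to show or report either event when a reaction to the puncture is most likely to be looked for.

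Two consequences follow. First, if the two events are expressed over all treated patients, the rates may be too low, and a low count may be read as reassurance that the data do not give. Second, the ability to report discomfort rises with GCS, which is a primary outcome. If the arms regain consciousness at different speeds, the chance of detecting discomfort differs between them, and reported discomfort could rise simply because patients wake sooner. Safety is part of the objective in section 1, so the point bears on a stated aim.

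**Working it through.** There is no stated figure to reproduce. The check sets the sections side by side and then illustrates the possible size.

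**Step 1: each named event against the entry criterion.**

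| Named event (2.4) | How it is detected | Depends on consciousness? |
|---|---|---|
| Hematoma | Examination | No |
| Local infection | Examination | No |
| Syncope | Visible loss of consciousness | Yes |
| Any feelings of discomfort | Patient's own report | Yes |

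Two of the four depend on the state that section 2.2.2 requires to be disturbed.

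**Step 2: do other provisions close the gap?** The list is open, and the general rule covers any adverse event resulting from THJP. That rule works only after someone has noticed an event and attributed it to the puncture. In a poorly responsive poisoned patient, a fall in blood pressure or GCS is easily put down to the poisoning. GCS and vital signs are measured at the right times, but sections 2.4.1 and 2.4.2 name them only as outcomes. Nothing in the article makes a deterioration in them a safety event.

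**Step 3: illustration of size.** Inputs: 31 THJP patients (section 2.5); u, the share who cannot be assessed, is not given and is assumed. Assessable patients m = 31 × (1 − u), rounded. With zero events among m patients, the exact one-sided 95% upper limit is 1 − 0.05^(1/m). If unassessable patients were counted as event-free and had the same true rate as the others, observed rate = true rate × (1 − u). A true rate of 10% is assumed for the last column.

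| u (assumed) | m | Upper limit, zero events | A true 10% would appear as |
|---|---|---|---|
| 0% | 31 | 1 − 0.05^(1/31) = 9.2% | 10% |
| 25% | 23 | 1 − 0.05^(1/23) = 12.2% | 7.5% |
| 50% | 16 | 1 − 0.05^(1/16) = 17.1% | 5.0% |
| 75% | 8 | 1 − 0.05^(1/8) = 31.2% | 2.5% |

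Across u from 0 to 100%, the observed rate runs from the true rate down to zero. The article gives nothing that narrows this range.

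**The case against.** The strongest reply is that the article leaves more room than the list suggests. Section 2.2.2 asks for disturbed consciousness, not coma, so a partly conscious patient may complain or may visibly lose consciousness further. Safety is assessed through 4 hours, by when a patient who has woken may report discomfort that persists. The list is open, a general adverse-event rule stands beside it, and vital signs are taken at the same visits. Coding of unassessable items and choice of denominators are matters that a condensed article may leave to the full protocol, the analysis plan or the case report form.

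Much of this stands, and it rules out stronger readings. A reader might infer that syncope and discomfort cannot be detected at all, that unconscious patients will be counted as event-free, that a circulatory reaction could never become a safety event, or that the safety objective cannot be answered. The article supports none of these. It sets no minimum severity and says nothing about how unassessable patients are coded. The general rule admits a circulatory reaction that is attributed to THJP, and two named events remain fully examinable.

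The choice of named events does not fall to a later document: the article states it, and two of the four suit this population poorly. An analysis plan can set a denominator, but it cannot recover whether a patient was able to answer if that was never recorded. The general rule also still depends on attribution.

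**Conclusion.** The point holds in a limited form. Syncope and discomfort can be ascertained only in part in patients selected for disturbed consciousness and treated on admission, so rates over all 31 THJP patients may be too low. The amount cannot be computed from the article, because neither the baseline GCS distribution nor the share of unresponsive patients is given. The figures of 9.2% (31 assessable) and 17.1% (16 assessable) show how far the meaning of a zero count could shift. They rest on an assumed share and an assumed zero result, and they do not predict this trial. Hematoma and local infection are unaffected.

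**What to change.** Amend section 2.4 as follows.

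- Keep the four named events and the general adverse-event rule. Syncope remains a valid event for patients who are awake or who wake.
- At each Table 1 visit, record whether the patient could be assessed for syncope and for discomfort. Report these two events by arm and time, with assessable patients as the denominator and that number shown.
- Add as safety events a deterioration from the previous assessment in GCS, blood pressure, pulse or respiration. The investigators set the thresholds in advance. Count these events per patient in both arms, whatever the attribution.

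The cost is protocol wording, an assessability item at each visit and a derived listing from data already scheduled. No new visit or procedure is needed. There are two downsides. The rates of syncope and discomfort will rest on fewer patients, and they describe only those who could be assessed. The added events will partly reflect the poisoning itself, so they must be read as a comparison between arms and not as a THJP event rate.
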